Prior to the second meeting, the contact person must arrange a meeting with the supplier/manufacturer of the selected ergonomic measure. Furthermore, a test environment must be arranged to facilitate the ability to acquire experience working with the chosen ergonomic measure. During the second meeting, construction workers will be able to get instruction and training on the ergonomic measure by an expert in a test environment (step 4). The expert may be a worker within the company who is familiar with the ergonomic measure, or the supplier of the ergonomic measure. Interventions regarding any hindrances on the use of the ergonomic measures will be discussed. In addition, instrumental help through a self-performed cost-benefit analysis of the ergonomic measure by the ergonomics consultant will be done to gain insight into the financial consequences for the companies.

The third meeting is intended to test the ergonomic measure in daily practice (step 5). Prior to this meeting, the interventions on the hindrances must have been carried out and preconditions for the test location in practice must have been formulated. During the third meeting, experiences of the ergonomic measures in daily work will be discussed. This results in interventions on hindrances in, and adaptations of, the preconditions of daily practice.

The interventions on hindrances in, and adaptations of, the preconditions will form the input for the final meeting and the last step (step 6). In this meeting, the test in practice will be evaluated and a choice will be made regarding whether the ergonomic measure will be implemented. An implementation strategy will be drawn up for the construction company, based on three levels: measure, e.g. buying or hiring the measures; behaviour, e.g. training of all construction workers; and organisation, e.g. deciding in which projects the ergonomic measure will be used. In addition, all four meetings will be evaluated, and members of the steering committee will be asked whether all four meetings are useful.

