The tenth email contact provides the agenda for the fourth meeting. Based on the test in daily work, a discussion will take place regarding whether the ergonomic measure will be implemented. In addition, points of interest will be defined for the further implementation. During the 11th email contact, an implementation strategy will be drawn up for the construction company based on three levels: measure, e.g. buying of hiring the measures; behaviour e.g. training of all construction workers; and organisation, e.g. deciding in which projects the ergonomic measure will be used (step 6).

After drawing up the implementation strategy, the process will be evaluated in email contact 12. Of each e-mail contact, the contact person will be asked whether the protocol is useful for the implementation of ergonomic measures. The 13th and final email contact contains the ending of the PE process.

After each meeting of the steering committee, all construction workers of the chosen occupations will be informed about the process of the intervention. In this manner, construction workers who are not part of the steering committee will be able to provide input throughout the entire intervention. The information obtained from each assignment given in each email contact will be returned by email to the ergonomics consultant. In each subsequent email contact of the ergonomics consultant, feedback will be given on the obtained information by the ergonomics consultant to the contact of the steering committee.

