#### Primary

The use of ergonomic measures is the primary outcome measure and is defined as whether ergonomic measures are used during the last two months by the individual construction workers. The ergonomic measures are defined in four clusters: 1) mechanical measures for horizontal or vertical transportation, such as a crane, 2) ergonomic measures for raising equipment or materials, such as a raised mortar hod, 3) ergonomic measures to adjust working height on the worksite, and 4) ergonomic handtools. Construction workers will be asked at baseline and after six months whether they used ergonomic measures during the last two months during their work (yes or no). Examples of the ergonomic measures are adjusted for the different occupations.

In addition, construction workers are asked at the end of the intervention how many days they could and did use the implemented ergonomic measure during the previous 10 working days.

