#### Economic evaluation

A cost-benefit analysis for each participating construction company will be made. At baseline, demographic characteristics of the employees with respect to sick leave will be assessed for the construction companies. The costs of the intervention will be assessed at the end of the intervention by multiplying the time spent by the ergonomics consultant with the hourly costs. In addition, at the end of the intervention, the director of the construction companies will be asked about the costs regarding employing the ergonomic measures and additional energy and the maintenance costs of the ergonomic measures. Furthermore, the director is asked if the production per working hour changed by using the ergonomic measure.

On the benefit side, construction workers will be asked at the end of the intervention how many days they could and did use the ergonomic measure during the previous 10 working days. In addition, construction workers are asked how they judge their physical work demands compared to working without the ergonomic measure. These three questions will provide a benefit for reducing risk factors for work-related musculoskeletal disorders. Another benefit aspect will be the change in production per working hour and change in quality of the work.

With the help of the Dutch Economic Institute of the Construction Sector, the above-mentioned aspects on the company level and on the individual worker level will result in a cost-benefit analysis for each construction company.

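### In companies whose guidance runs close to six months, the cost, production and use items are asked before the step 6 decision can be carried out, so they largely describe the try-out or planned costs

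*Protocol article*

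**What the plan says.** **Economic items.** The Economic evaluation section under Outcome measures sets the time of the cost items: "at the end of the intervention, the director of the construction companies will be asked about the costs regarding employing the ergonomic measures". Energy and maintenance costs are part of the same enquiry, and the production item follows directly: "Furthermore, the director is asked if the production per working hour changed by using the ergonomic measure". The use data come from a separate source, the workers, at the same point in time: "construction workers will be asked at the end of the intervention how many days they could and did use the ergonomic measure", looking back over 10 working days. They also compare their physical work demands with working without the measure. The Primary outcome section words the use item as "how many days they could and did use the implemented ergonomic measure during the previous 10 working days". Consultant cost is time spent multiplied by an hourly rate, also totalled at the end.

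**Order of the steps.** In the face-to-face strategy, "The third meeting is intended to test the ergonomic measure in daily practice (step 5"). At the fourth and final meeting, step 6, "the test in practice will be evaluated and a choice will be made regarding whether the ergonomic measure will be implemented". The implementation strategy, covering purchase or hire, training of all workers and choice of projects, is drawn up at that same meeting. In the e-guidance strategy, implementation is discussed at the fourth meeting, whose agenda is email 10. In email 11 of 13, "an implementation strategy will be drawn up for the construction company based on three levels". Emails 12 and 13 evaluate and close the process.

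**Time frame.** The Interventions section gives six months as the maximum duration of guidance. Outcome measures puts baseline at the start of the intervention and the only follow-up questionnaire six months later. The Economic evaluation section under Statistical analyses plans a descriptive calculation per company, with no projection from the test to later routine use.

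**The concern.** The use item presupposes that a measure has been implemented, yet the plan's own steps reach that decision only at the end of guidance. Consultant time is essentially complete by then, so the guidance cost is counted in full. The use that should produce the benefit may have only a test behind it. The director's answer may also mix periods, because a price for a planned purchase can end up next to use and production observed during a test.

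Cost-benefit is the third element of the study objective. The Background section expects face-to-face guidance to cost more and to repay this through greater use of measures. A calculation that stops at the decision cannot show whether it does.

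**Working it through.** The plan states no figure on this point, so the check compares the order of steps with the times of measurement.

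**1. Events side by side**

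| Event | Face-to-face | E-guidance |
|---|---|---|
| Test in daily work (step 5) | Meeting 3 | Meeting 3 (email 7), adaptations in emails 8 and 9 |
| Whether to implement | Meeting 4, the last | Meeting 4 (email 10) |
| Plan for purchase or hire, training, projects (step 6) | Meeting 4 | Email 11 |
| Process evaluation | Meeting 4 | Email 12 |
| Closing | none listed | Email 13 |
| Director and worker economic items | End of the intervention | End of the intervention |
| Later economic data | none described | none described |

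**2. What the look-back needs.** Ten working days are 10/5 = 2 weeks. Six months are about 26 weeks, or 26 × 5 = 130 working days, so the window is 10/130 = 7.7% of the period. Let *g* be the week of the step 6 decision and *d* the weeks needed for delivery and training. The document does not give *d*. If the items are asked at month six, the window contains only rolled-out use when

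26 − *g* ≥ 2 + *d*, that is *g* ≤ 24 − *d*.

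Even with *d* = 0, the decision must fall by week 24. When guidance uses its full allowance in the face-to-face strategy, *g* = 26 and the time left is 0.

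**3. If the end means the last contact.** In the face-to-face strategy the decision meeting is the last guidance contact, so the gap is 0 whatever the duration. In e-guidance the gap is the time taken by emails 11 to 13, which is not stated.

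**4. Is near-full duration the expected case?** Six months is stated as a maximum. The competence item in the Process evaluation is nevertheless asked after six months of guidance have been completed, and the Limitations section treats six months as the set duration. Near-full length is therefore a reasonable working expectation, though not a certainty. For companies that finish earlier, time since the decision is 26 − *g* under the month-six reading. It varies between companies and nothing in the text fixes it.

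**5. Link to the primary analysis.** The sample size (113 per group; 113 × 1.24 = 140.12, stated as 140) uses none of these items and is unaffected.

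**The case against.** The strongest reply is that the timing does not exclude real costs and real use.

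- **Early finishers.** Six months is a maximum. If the items are asked at month six, a company that finishes sooner has time after its decision. This stands, so it cannot be said that every company's result describes the try-out.
- **Spending before step 6.** A reader might infer that nothing has been bought when the director is asked. The text does not say so. Budget is reserved in step 1a, the fourth e-guidance email includes an agreement with a supplier to acquire the measure, and step 5 is use on a real site. What step 6 fixes is the roll-out.
- **Quality of the director's answers.** The cost item is not limited to money already spent, and a cost-benefit analysis of the measure accompanies meeting 2. Directors can quote prices and need not guess. This stands, but it leaves planned cost paired with test use.
- **The wording could and did.** Asking both allows use to be read relative to availability, which partly answers incomplete roll-out. It does not turn test use into routine use.
- **A bias between strategies.** A reader might infer that e-guidance companies get more time after the decision, because three emails follow meeting 4 against no contact in face-to-face. This requires the end to mean the last contact. The emails have no stated spacing, and two of them carry tasks that face-to-face completes inside meeting 4. A lag is possible, but its size is unknown.
- **Condensed article.** The exact date of the end may be in the full protocol. That may settle the date. It would not change the order of steps, which the article states.

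**Conclusion.** The concern holds in a limited form. For a company whose guidance runs to or near six months, the cost, production and use items cannot reflect rolled-out use. They largely describe the step 5 test or planned costs, and full guidance cost is set against them. For a company that finishes earlier, the items may include real use, but over an unfixed time since the decision.

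The number of companies affected cannot be derived, and all 12 is only an upper bound. A reader might want to put a factor on the understatement of benefit. The documents give no days of use for either period, and use in a supervised test could even exceed later use, so neither a factor nor a direction is supported. A difference between strategies caused by timing alone is not shown either.

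The conclusion assumes that the production item shares the timing of the director's cost items, and that no later economic data are collected, since none are described. It is a cheap improvement to a descriptive part of the study.

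**What to change.** 1. Define the end of the intervention by one date rule that applies to both strategies.
2. For each company, record whether and when the measure was implemented, and mark each cost as incurred or planned.
3. Present use and production separately for companies with at least 10 working days of rolled-out use and for those still in try-out. For the latter, limit the cost-benefit conclusion to costs and benefits up to the decision.
4. Where feasible, ask the director's items and the short days-of-use and work-demand items at one fixed interval after the final steering committee meeting, the same in both strategies.

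Items 1 to 3 cost a few extra recorded fields per company. Item 4 is more debatable: it means 12 short director contacts, one page of worker questions at a later date and somewhat later economic results. The primary outcome, its analysis and the sample size stay as they are.

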### Sample size

The sample size is based on detecting a difference in the use of a new ergonomic measure between the face-to-face guidance strategy and the e-guidance strategy. In a study of Jensen and Friche [6], it was found that daily use of new introduced construction working methods could be at least 10%. We have decided that a 15% absolute difference in use of newly introduced ergonomic measures between the two guidance strategies is a realistic and relevant difference.

Based on a power calculation using the Nquery Advisor software [25], 113 workers per group must be included for a difference of 15% (from 10% to 25%) with an alpha of 0.05 (two-tailed) and a power of (1-beta) = 0.80. A small cluster effect on the use of ergonomic measures at the level of the construction companies will be anticipated (ICC = 0.01). The construction companies have influence on the use of ergonomic measure by their employees, therefore there is a correlation between company and its employees. Since there is no interaction between the participating companies and because of the different characteristics of the companies (e.g. culture within the company, different trades) the assumption is that the correlation between the companies will be small. Based on the inclusion criteria, the assumption is made that the average number of construction workers (n) within a construction company is on average 25. This results in a cluster effect of 1.24 (1 + ((n-1) × ICC) and an adjusted sample size of 140 per group. To reach this sample size, we must include six construction companies per group.

### Randomisation

The construction companies will be block randomised with a block size of two with the help of nQuery Advisor 7, a computer generated randomisation table. The independent variable for this randomisation is the sequence of inclusion. The first construction company participating within an occupation will be randomly assigned to the face-to-face guidance strategy group or the e-guidance strategy group. The second company participating within the same occupation will be assigned to the opposite strategy group. The implementation strategy makes blind group assignment impossible for the participating companies, the ergonomics consultants and the observers of the steering committee meetings.

Based on practical constraints, the ergonomics consultants divided the Netherlands into a northern part and a southern part. Construction companies in the northern part of the Netherlands who are assigned into the face-to-face guidance strategy group are allocated to ergonomics consultant 1, and construction companies in the southern part to ergonomics consultant 2. Construction companies assigned into the e-guidance strategy group are randomly assigned to ergonomics consultant 1 or 2.

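### Consultants are assigned by region in the face-to-face arm but at random in the e-guidance arm, so uneven north/south recruitment gives the two strategies different expected consultant mixes

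*Protocol article*

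**What the plan says.** All of the relevant rules stand in the protocol article, mainly under Randomisation.

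- **Strategy.** "The construction companies will be block randomised with a block size of two". Blocks are formed within occupation by order of inclusion: "The second company participating within the same occupation will be assigned to the opposite strategy group". Neither region nor consultant is a blocking factor.
- **Regions.** "Based on practical constraints, the ergonomics consultants divided the Netherlands into a northern part and a southern part".
- **Consultant, face-to-face arm.** Northern companies "who are assigned into the face-to-face guidance strategy group are allocated to ergonomics consultant 1"; southern ones go to consultant 2.
- **Consultant, e-guidance arm.** "Construction companies assigned into the e-guidance strategy group are randomly assigned to ergonomics consultant 1 or 2". No ratio or restriction is given.
- **Size.** Under Sample size: "To reach this sample size, we must include six construction companies per group".

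The Effect evaluation part of Statistical analyses names the company as the source of dependency between workers. The E-guidance strategy section describes guidance by 13 emails and keeps the consultant out of the committee meeting that it describes.

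**The concern.** Two people deliver the whole intervention, and the rule that decides who delivers it differs by arm. In the face-to-face arm the consultant mix follows the regional split of the recruited companies. In the e-guidance arm it is expected to be half and half whatever that split is. If most companies come from one region, one consultant carries more of the face-to-face arm than of the e-guidance arm. This imbalance is built in by the rule after strategy has been randomised, and enrolling more workers would not remove it.

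The consultant matters on the protocol's own terms. The Background attributes the expected advantage of face-to-face guidance to the consultant being present, and the Process evaluation section measures consultant competence. If one consultant is better at getting measures adopted, that difference is partly read as a difference between strategies. The Economic evaluation costs guidance from consultant time, so the cost comparison is exposed in the same way.

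Within the face-to-face arm, consultant and region are also the same variable, so a consultant effect cannot be told apart from a regional one there.

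**Working it through.** **The plan's own figures.** 10% against 25%, two-sided alpha 0.05 and power 0.80 give 113 per group with continuity correction (100 without). Then 113 × (1 + 24 × 0.01) = 140.12, and 140.12 / 25 = 5.6, so six companies per arm. These reproduce and are not in question. They supply the 12 companies and the 15-point target used below.

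**Inputs.** From the article: 12 companies, six per arm, and the two consultant rules. Assumed: K northern companies (no split is given), 1:1 random assignment in the e-guidance arm, and a difference d between consultants in their effect on use. Strategy is taken as independent of region and, for simplicity, the occupation blocks are ignored.

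**Expected gap.** The number of face-to-face companies with consultant 1 is hypergeometric (12, K, 6), with mean 6K/12. The e-guidance number is binomial (6, 0.5), with mean 3. The expected gap in consultant 1's share is K/12 - 0.5, and the expected bias in the strategy contrast is d × (K/12 - 0.5).

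| K of 12 in the north | Expected consultant 1 companies, face-to-face vs e-guidance | Gap (points) | Probability that the counts differ by 3 or more | Bias (points) for d = 5 / 10 / 15 |
|---|---|---|---|---|
| 6 | 3 vs 3 | 0 | 9.5% | 0 / 0 / 0 |
| 7 | 3.5 vs 3 | 8.3 | 11.2% | 0.4 / 0.8 / 1.25 |
| 8 | 4 vs 3 | 16.7 | 16.4% | 0.8 / 1.7 / 2.5 |
| 9 | 4.5 vs 3 | 25 | 24.8% | 1.25 / 2.5 / 3.75 |
| 10 | 5 vs 3 | 33.3 | 36.2% | 1.7 / 3.3 / 5.0 |

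If the south predominates, the gaps have the same size and the opposite sign.

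**Region.** The expected north/south difference between arms is zero for every K. Only chance imbalance arises.

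**Comparing rules.** Let s = K/12. The variance of the northern share in one arm, drawn without replacement, is s(1 - s)/11. The root mean square (RMS) gap in consultant 1's share is:

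- plan: √[(s - 0.5)² + s(1 - s)/11 + 0.25/6]
- region rule in both arms: 2√[s(1 - s)/11]
- matching within occupational pairs, with the e-guidance company enrolling first in half of six complete pairs and then taking its own region's consultant: the region-rule value divided by √2

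At K = 9 the plan gives √(0.0625 + 0.0170 + 0.0417) = 0.348, the region rule 2√0.0170 = 0.261, and pair matching 0.261/√2 = 0.185.

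| K | Plan | Region rule in both arms | Pair matching |
|---|---|---|---|
| 6 | 0.254 | 0.302 | 0.213 |
| 7 | 0.266 | 0.297 | 0.210 |
| 8 | 0.299 | 0.284 | 0.201 |
| 9 | 0.348 | 0.261 | 0.185 |
| 10 | 0.407 | 0.225 | 0.159 |

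The region rule and pair matching both have an expected gap of zero at every K.

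**The case against.** The best defence is that the problem is conditional and may be small. At an even split there is no expected gap. Both consultants can serve both arms, so the confounding is partial. A 15-point difference between consultants is a high assumption: it equals the whole target difference and sits badly with the planning ICC of 0.01. At mean use of 17.5%, two equally used consultants 15 points apart would alone imply an ICC of (0.15²/4) / (0.175 × 0.825) = 0.039. If all of an ICC of 0.01 came from consultants, they would differ by 2√(0.01 × 0.175 × 0.825) = 7.6 points, giving 1.9 points of bias at 9 of 12. The consultants also wrote both protocols from one six-step approach, and delivery is checked against 31 performance indicators. All of this stands and limits the likely size. It does not explain why the two arms need different rules.

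Three stronger readings are tempting, and the document supports none of them.

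- A reader might infer that region is confounded with strategy. It is not, because strategy is allocated within occupation by order of inclusion, without reference to region.
- A reader might infer that using the regional rule in both arms is always at least as good. With 12 companies it has the larger RMS gap at 6 or 7 northern companies (0.302 against 0.254, and 0.297 against 0.266). It also makes consultant and region identical in both arms.
- A reader might count the absence of a consultant term in the model as an omission. That may be left to a statistical analysis plan that is not shown. The point here is the assignment rule, which the article does fix.

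**Conclusion.** The point holds in a limited form. The two consultant rules make the expected consultant mix differ between strategies whenever north/south recruitment is uneven, by K/12 - 0.5 under 1:1 random assignment. Any consultant effect then enters the strategy contrast. The size and direction cannot be determined from the document. Over the assumed range of 5 to 15 points between consultants, the bias at 9 of 12 northern companies is 1.25 to 3.75 points, or 8% to 25% of the 15-point target, and at 6 of 12 it is zero. This is no proof that the comparison will be misleading. It is an avoidable weakness: the regional split rests on practical constraints, and guidance by email gives no evident reason to treat the e-guidance arm differently.

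**What to change.** Replace random consultant assignment in the e-guidance arm with matching inside the occupational pair. If the face-to-face partner is already enrolled, the e-guidance company gets that partner's consultant. Otherwise it gets the consultant for its own region. Report the number of companies per consultant in each arm.

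This removes the expected gap at every split and, under the stated assumptions, gives a smaller RMS gap than the current rule at every K tabulated. It needs a sentence or two under Randomisation and no travel.

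There are two small downsides. Consultant and region become harder to separate in the e-guidance arm, where random assignment now keeps them apart. Pairs in which the e-guidance company enrols first may stay unmatched, as will any company without a partner in its occupation, a situation that the Limitations section already foresees.
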